### Secondary objectives

The secondary objective is to determine the treatment effect on attitudes towards stuttering among Grade 7 participants based on the SROM subscales of PSD, SP and VI.

It is hypothesized that there may be an improvement in each subscale but it is unknown which will show a greater improvement. These subscales will be compared to the control group treatment effect. This study will also evaluate the areas of interaction between peers that exist and may be self-perceived.

The subgroup analysis objective is also to determine the primary objective between and across the lower and higher quintile school clusters. Previous studies have shown that the lower quintile schools are more negative than the higher quintile schools initially [19]. It is hypothesized that both quintiles in the intervention groups will yield positive shifts in treatment effects when compared to the control group while it is unknown which quintile will be most positive, or where the greatest shifts will occur.

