### Sample size with power analysis

The sample size calculation was based on previous CCR intervention studies [18, 19, 26]. With the proposed sample size of *n* = 350 students (*k* = 10 schools) in each of the two groups (i.e. assuming a 1:1 allocation ratio), the study will have the power of 80% to yield a statistically significant result using a generalised estimating equations (GEE) model (assuming an intention-to-treat (ITT) principle for the analysis) of the difference between mean in SROM global scores at 6-month adjusting for baseline (pre-intervention) SROM global score at alpha = 0.05. This computation is based on a pilot study [19] which assumes that SROM global scores are normally distributed, the mean difference is 5.25 (corresponding to mean of 77.91 (for the intervention group) versus 72.66 (for the control group)) and the common within-group standard deviation is 11.90 and an ICC (intra-school correlation coefficient) of 72.70.

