### Assignment of interventions

#### Allocation: sequence generation, allocation concealment mechanism and implementation

The statistician will generate the computerised allocation sequence. The random allocation ratio will be 1:1 while the randomisation will be stratified into 2:1 where the lower quintile has a higher number of assignments of participants per school when compared to the higher-quintile schools. The written allocation of the assignment of participants will be sealed in an envelope which contains identification numbers. These identification numbers will be distributed across the lower- and higher-quintile schools. A sufficient number of schools will be included to meet the targeted sample size. The researcher will open the envelope to determine the allocation of schools. The stratification of the sample will occur in the following order; mixed-gender schools, schools within quintiles 2 and 3 and 4 and 5 and finally according to the eligibility characteristics and restrictions.

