#### Statistical methods

The analysis will follow the intention-to-treat (ITT) principle and will be reported according to CONSORT guidelines [32]. The GEE will be used to compare the groups on global SROM and subscales to address the primary objective. Assuming an exchangeable correlation structure within a school, GEE will allow for possible clustering within a school to be accounted for. The unit of analysis will be the grade-7 student. The results will be reported as estimate of the difference between groups, 95% confidence interval and associated *p* value. All *p* values will be reported to three decimal places with those less than 0.001 reported as *p* < 0.001. The criterion for statistical significance will be set at alpha = 0.05. The subgroup hypothesis will be tested by adding an interaction term of the quintile group (lower versus higher) × intervention (CCR versus usual practice) in the model. Similarly, this analysis will be used to address the secondary objective by analysing the PSD, VI and SP constructs on the SROM. The subgroup analysis will use this method of analysis to address the subgroup analysis between and across the quintiles. See Additional file 1: Table S1 for a summary table of the objectives, outcomes, hypotheses and methods of analysis.

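### The quintile × intervention interaction tests whether the two quintile effects differ, not the stated hypothesis that both quintile groups benefit

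*Protocol article*

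**What the plan says.** The Secondary objectives section of the protocol article sets a subgroup objective, "to determine the primary objective between and across the lower and higher quintile school clusters". Its hypothesis has two parts. The first is directional: "both quintiles in the intervention groups will yield positive shifts in treatment effects when compared to the control group". The second leaves the comparison open: "it is unknown which quintile will be most positive, or where the greatest shifts will occur".

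The Statistical methods section assigns one test: "The subgroup hypothesis will be tested by adding an interaction term of the quintile group" (lower versus higher) by intervention (CCR versus usual practice), within the generalised estimating equations (GEE) model. It adds: "The subgroup analysis will use this method of analysis to address the subgroup analysis between and across the quintiles". The text names no effect estimate within either quintile group.

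The Sample size section plans "350 students (*k* = 10 schools) in each of the two groups" and claims 80% power for the main comparison only. The allocation section says that "the randomisation will be stratified into 2:1 where the lower quintile has a higher number of assignments of participants per school". The number of schools per quintile group and arm is not given.

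**The concern.** The article ties a named hypothesis to a named test, and for the first part of the hypothesis the two do not match. An interaction coefficient is the difference between the two stratum effects. It carries no information on whether either effect is above zero.

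At stake is the subgroup conclusion on no-fee versus fee-paying schools. With only the interaction to report, the investigators would have no planned result for or against benefit in both groups. A non-significant interaction would also be open to misreading as equal benefit, although the test is likely to be non-significant over a wide range of true differences.

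**Working it through.** **1. Hypothesis against test.** Let L and H be the CCR-minus-control effects in lower and higher quintile schools. The hypothesis is L > 0 and H > 0. The interaction tests L − H = 0. The values below are illustrative multiples of the planning effect of 5.25.

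| L | H | L − H | Do both benefit? |
|---|---|---|---|
| 0 | 0 | 0 | No |
| 5.25 | 5.25 | 0 | Yes |
| 5.25 | 0 | 5.25 | No |
| 10.50 | 5.25 | 5.25 | Yes |

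Rows 1 and 2 have the same interaction and opposite answers to the hypothesis. So do rows 3 and 4. This step needs no assumption about variance or school numbers.

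**2. The plan's own power figure.** Inputs from the Sample size section: 350 students and 10 schools per arm (35 per school on average), difference 5.25, SD 11.90, alpha 0.05 (two-sided assumed), ICC printed as 72.70. A correlation cannot exceed 1, so the 80% cannot be reproduced as printed. With design effect DE = 1 + 34 × ICC, SE = √(2 × 11.90² × DE / 350) and no gain from baseline adjustment:

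- ICC 0.0727: DE 3.472, SE 1.676, power 87.9%.
- ICC 0.727: DE 25.718, SE 4.562, power 20.9%.

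Neither gives 80%. Taking the 80% as given instead, SE_main = 5.25 / (1.96 + 0.84) = 1.874 (unrounded quantiles). That corresponds to DE 4.340 and ICC (4.340 − 1)/34 = 0.098. The 0.098 is back-solved and does not appear in the article.

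**3. What the interaction could show if the 80% holds.** Let p be the lower-quintile share of schools, the same in both arms. Then SE_int = SE_main / √(p(1 − p)). The difference detectable with 80% power is 2.80 × SE_int by the normal approximation, or (2.120 + 0.865) × SE_int by t on 16 df (20 schools less 4 cells).

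| Lower:higher schools per arm | SE_int | Detectable, normal | Detectable, t | Power at 5.25 (normal / t) |
|---|---|---|---|---|
| 5:5 | 3.748 | 10.50 (2.00×) | 11.19 (2.13×) | 28.8% / 26.0% |
| 6:4 | 3.825 | 10.72 (2.04×) | 11.42 (2.17×) | 27.8% / 25.2% |
| 7:3 | 4.089 | 11.46 (2.18×) | 12.20 (2.32×) | 24.9% / 22.6% |

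The t columns pair a main-effect SE from the normal approximation with a t-based interaction. With t used for both (SE_main 1.772 on 18 df), the multiples are 2.01 to 2.20. If the 2:1 means pupils per school with 5:5 schools, the multiple is 2.03 by the normal approximation.

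**4. Range over the ICC.** If the ICC is set directly rather than through the 80%, the detectable interaction over the same splits is 1.79 to 1.95 times 5.25 (normal) or 1.91 to 2.08 (t) at ICC 0.0727. At ICC 0.727 it is 4.87 to 5.31 (normal) or 5.19 to 5.66 (t).

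**5. Precision of the within-quintile effects.** The SE within a stratum is SE_main / √p for lower and SE_main / √(1 − p) for higher. With the 80% taken as given, power to show 5.25 (normal approximation) is 51% in each stratum at 5:5, 58% and 43% at 6:4, and 65% and 34% at 7:3. Power to show it in both is 22 to 26%.

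**The case against.** The strongest reply is that the subgroup aim is wider than the clause on both groups benefiting. The objective covers comparison between quintiles, the Study setting section says the trial aims to compare the treatment effect in the two groups, and the Subgroup analyses section notes that between-quintile findings are lacking. For that comparison the interaction is the standard and correct test. This stands. A reader might infer that the named test leaves the subgroup objective wholly unanswered, but the article does not support that.

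A second reply is that within-quintile effects are linear combinations of the planned model, that results are to be given as estimates with 95% confidence intervals, and that a supplementary table of hypotheses and methods is not shown. The contrasts may be listed there. What remains is that the article's own text assigns the subgroup hypothesis to the interaction, and that pairing is wrong for its first part wherever the contrasts are specified.

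A third reply concerns power. A factor of about two is what any evenly split trial powered on its main effect would show, and the article claims no power for the subgroup. This also stands, so the power figures are context and not a separate defect.

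**Conclusion.** The mismatch holds. The interaction cannot confirm or refute benefit in both quintile groups, whichever way it comes out. The point concerns one part of a secondary subgroup objective and does not touch the primary analysis.

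The size of the power limitation rests on assumptions: the stated 80% main-effect power, two-sided alpha of 0.05, equal school sizes, a common SD and ICC across strata, and a split between 5:5 and 7:3. On these, 80% power needs a difference of about 2.0 to 2.3 times 5.25, and power at 5.25 is about 23 to 29%. The multiple moves to about 1.8 to 2.1 at ICC 0.0727 and to about 5 at 0.727.

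Three stronger readings are not supported:

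- That the trial cannot detect a smaller difference. Power below 80% is low, not zero.
- That there are only 3 or 4 higher-quintile schools per arm. The 2:1 is worded as participants per school, no school split is given, and the factor of about two already arises at 5:5.
- That the investigators will report a null interaction as equal effect. The article does not say so; the wording merely leaves room for it.

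**What to change.** In Statistical methods, split the subgroup analysis in two.

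- For the hypothesis that both quintile groups benefit: from the same interaction model, estimate the CCR-minus-control effect within lower and within higher quintile schools, each with a 95% confidence interval. Use a small-sample correction to the GEE standard errors, since there are only about 20 schools.
- For the between-quintile question: keep the interaction, report it as an estimate with a 95% confidence interval, and state that a non-significant result will not be read as equal effect.

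The cost is two contrasts from a model already planned and some wording, with no new data or schools. The subgroup claim becomes more modest, because the within-quintile estimates will themselves be imprecise (step 5 of the working).

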#### Subgroup analyses

Subgroup analyses between quintiles and cluster analysis between the sample has been explored in a previous feasibility study [19]. It was found that schools behaved as clusters and thus it was appropriate to administer and evaluate participants within clusters [19], supporting a group-based approach. There are no findings between quintiles using the CCR intervention in such a large-scale trial and thus this study aims to include this aspect of analysis.

#### Nested studies

A few challenges were highlighted in the previous study such as poor retention of participants [19]. It is unknown what other challenges may arise. It is for this reason that the researcher, research assistants and teachers will be required to have logbooks in which detailed accounts and experiences are documented.

### Monitoring

#### Data monitoring and auditing

The data will be captured, audited, monitored and secured by a team of research assistants along with a statistician who will form the Data Monitoring Committee. The research assistants and statistician have no competing interests.

## Discussion

### Harms

The teacher will be consulted prior to data collection to identify whether there is a CWS in the classroom. The CWS may choose to not participate or to not have the intervention run in their classroom. Teachers will also be asked to note any concerns. Any participants requiring counselling will be referred to a psychologist by the researcher. However, in all the previous studies, no concerns or need for counselling have been identified or required [18, 19]. In fact, the studies showed minimal improvements in the ratings of attitudes at 1 month post intervention while more prominent results were observed at 6 months post intervention [18, 19]. Other benefits include access and training to the CCR intervention for all schools and teachers. The benefits, therefore, outweigh any potential risks that may be experienced. The data will be collected at schools where participants are comfortable, and the use of logbooks will be vital in informing if any harms are noted.

### Ancillary and post-trial care

Post-trial care will include the provision of the CCR intervention and training to control group teachers. No other harms are anticipated, as mentioned previously.

### Dissemination policy

The primary researcher will provide findings of the study to each school, principal and its teachers. The researcher will provide this in a format that is most suitable and preferential for each school (e.g. written report, face-to-face meeting, email or telephonic). They will also be given access to the article once the final findings are published.

### Trial status

This is protocol version 5 on 28 June 2016. The protocol was reviewed by the departmental and divisional reviewers at UCT. Following feedback, a rebuttal was submitted. Once the protocol was approved by the departmental and divisional reviewers, the protocol was sent to the FHSREC to obtain ethical approval. The protocol has, therefore, undergone a number of reviews. Recruitment began on the 31 January 2017.

## Abbreviations

CCR: Classroom Communication Resource
CONSORT: Consolidated Standards of Reporting Trials
CWS: Children who stutter
FHSREC: Faculty of Health Sciences and Research Ethics Committee
GEE: Generalised estimating equations
ICF: International Classification and Functioning of Disability
ITT: Intention-to-treat
LoLT: Language of learning and teaching
NNSSF: National Norms and Standards for School Funding
PATCS: Peer Attitude Towards Children who Stutter
POSHA-S: Public Opinion Survey of Human Attributes-Stuttering
PRS: Protocol registration and results system
PSD: Positive Social Distance
RCT: Randomised controlled trial
SP: Social Pressure
SPIRIT: Standard Protocol Items for Reporting in Trials
SROM: Stuttering Resource Outcomes Measure
TAB: Teasing and Bullying: Unacceptable Behaviour
UCT: University of Cape Town
VI: Verbal Interaction
